**Figure 2 F2:**
[figure not shown]
**PITSTOP suicide study design.** IAU, implementation as usual; PITSTOP suicide, professionals in training to STOP suicide; T0, admission; T1; 3 months after admission; TtT-e, e-learning supported train-the-trainer implementation.

### Measurement at patient level

#### Suicide ideation and suicide attempts

The primary outcome, suicide ideation, will be measured using the Beck Scale for Suicidal Ideation (BSS)
[28], a well-validated and widely used instrument. The BSS consists of 21 self-reported items. The first 19 items measure the severity of actual suicidal wishes and plans; item 20 assesses the number of previous suicide attempts; and item 21 assesses the severity of the last suicide attempt. Normally, if a patient scores 0 on items 1 through 5, items 6 through 19 are automatically scored 0, and the patient is directed to item 20. If the patient scores more than 0 on items 1 through 5, all items of the BSS are completed. In our study we asked patients to complete all 19 items, even if they scored 0 on items 1 through 5. By doing so, we hoped to be able to detect small differences in suicide ideation in patients with a low suicide trait. The overall score is computed by summing the scores of the first 19 items. The overall score ranges from 0 to 38; a higher score indicates a higher level of suicide ideation. Item 20 and 21 are not used to calculate the ideation score, but are used to assess the number and intensity of previous suicide attempts.

#### Treatment satisfaction

Treatment satisfaction will be assessed with four items established to measure the quality of therapeutic alliance. The first two items are: ‘How satisfied are you with your therapy?’ and ‘How would you evaluate your relationship with your therapist?’. These two items are rated from 0 to 10. Next, we will assess treatment satisfaction with reference to patients’ suicidal behavior: ‘Was there any attention for your suicidal thoughts during therapy?’ and ‘How did your therapist deal with your suicidal thoughts?’. These two items are scored on a four-point Likert scale ranging from: 1, very well, to 4, very poor. As the questions focus on the patient’s experience, these four items will only be administered at T1.

#### Cost-effectiveness

Costs incurred by patients during the course of the study will be measured with an adapted version of the Trimbos questionnaire for costs associated with psychiatric illness (TiC-P)
[29]. The TiC-P consists of two parts: part one measures direct medical costs (for example visits to a psychiatrist or a psychologist) and part two measures indirect costs (for example costs due to sick leave and productivity losses while being at work but not functioning optimally). If available, Dutch guideline prices will be used to value resource use
[30]. Medication use will be valued using prices of the Royal Dutch Pharmaceutical Society. Lost productivity costs will be calculated according to the friction cost approach (friction period 154 days) using the mean age- and sex-specific income of the Dutch population
[30]. Costs of the development of the intervention will be based on the salaries of the researchers for the development of the TtT-e program, material costs, implementation costs of the e-learning environment, and the costs of the production losses due to training of multidisciplinary teams.

#### Quality of life

Quality of life will be measured using the EQ-5D (EuroQol, Rotterdam, The Netherlands)
[31]. This is a five-item questionnaire with an additional visual analogue scale (VAS) developed to assess health-related quality of life. The five items represent the dimensions of mobility, self-care, usual activities, pain/discomfort, and anxiety/depression. Items are scored on a three-point Likert scale: 1, no problem; 2, some problems; and 3, extreme problems. The health states obtained from EQ-5D will be converted to utility scores using the Dutch EQ-5D tariff. Quality-adjusted life years (QALYs) will be calculated using the area-under-the-curve method with linear interpolation between time points. A VAS is also included to measure the patient’s self-rated health from: 1, best imaginable health state, to 5, worst imaginable health state.

### Inclusion and exclusion criteria

Departments are considered eligible for participation if they treat patients aged ≥18 years and if professionals consider a need for training in suicide prevention skills, and their management are willing to provide support including financial support for covering loss of production.

Since basic clinical skills, such as establishing a therapeutic alliance with the patient, are an important part of the training and e-learning, it is expected that patients who report no suicide ideation at baseline will benefit from the TtT-e program. Therefore, all patients irrespective of being suicidal at baseline will be included. Since admitted patients will often be affected by emotional and/or cognitive problems, patients who are emotionally and/or cognitively unable to complete questionnaires properly will be excluded. Whether a patient is able to enter the study will be left to the discretion of the staff.

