### Measurement procedure

At patient level, the preferred mode of data collection is by routine outcome monitoring (ROM), an online system by which data on the effectiveness of treatment in everyday clinical practice are systematically collected
[26]. In MHIs not using ROM, graduate students and/or research assistants will use paper and pencil questionnaires to collect data. The results from the graduate students/research assistants are expected to be comparable to the data collected via ROM. ROM also works with assistants to collect data and help participants to understand items/instructions
[26]. Using differential item functioning (DIF)
[27], we will investigate if the findings are indeed comparable, and control for any bias due to difference in data collection in the final analysis. By collecting data either via the ROM or graduate students/research assistants, we aim to reach all newly admitted patients in the participating departments. As the intervention focuses on fostering a working relationship with suicidal patients, the intervention is expected to be most effective during the first month of treatment. Therefore, patients will be assessed directly at admission (T0) and at 3 months after admission (T1) (Figure 
2). If a patient is discharged within 3 months, T1 will be arranged just before discharge. Measurements in the experimental departments will start immediately after all staff are trained. In the control departments, T0 will start when the department is informed of the allocation outcome. All eligible patients will be informed about the study and will be asked to provide written informed consent.

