### Randomization procedure

Eligible departments were clustered in pairs. It is assumed that similar types of patients treated for a similar duration of time are likely to be comparable. The first criterion for matching departments was the main diagnostic category of patients. For instance, a department that reported that 60% of the patients had a main diagnosis of depression was matched with another department that reported a comparable percentage of depressive patients. Within groups of comparable patient diagnoses, departments were matched with departments with comparable average treatment duration of patients. Members of matched pairs were randomly allocated to either IAU (internet, newsletter, books, publications, and congresses; control) or IAU with the TtT-e program (intervention). Randomization was performed by an independent researcher of the research institution (EMGO + Institute for Health and Care Research, Amsterdam, The Netherlands) who was not involved in the study. Table 
1 displays an overview of the types of departments, patient diagnoses, and results of the matching procedure. Healthcare professionals are aware of the allocation outcome, but patients are not.

**Table 1 T1:** Overview of the mental health institutions (MIHs), departments, main patient diagnoses, and results of the matching procedure

**MHI**	**Department**	**Average treatment duration of patients (days)**	**Main diagnosis**	**Condition**
Delfland	Inpatient	1,532	Depression	EXP
Delfland	Inpatient	1,308	Depression	CON
Delfland	Outpatient	624	Depression	EXP
Dimence	Outpatient	600	Depression	CON
Parnassia	Outpatient	21	Depression	CON
Parnassia	Inpatient	16	Depression	EXP
Delfland	Outpatient	740	Depression	CON
Parnassia	Inpatient	730	Depression	EXP
Pro Persona	Crisis	1	Depr/bord/crisis	CON
Pro Persona	Crisis	1	Depr/bord/crisis	EXP
Parnassia	Inpatient	250	Personality	EXP
Dimence	Inpatient	400	Personality	CON
Dimence	Crisis	1	Depr/bord/crisis	EXP
Parnassia	Crisis	1	Depr/bord/crisis	CON
Friesland	Outpatient	582	Depression	EXP
Friesland	Outpatient	814	Depression	CON
Friesland	Outpatient	743	Depression	EXP
Friesland	Outpatient	602	Depression	CON
Parnassia	Outpatient	90	Depression	EXP
Parnassia	Outpatient	21	Depression	CON
Viersprong	Personality	240	Personality	CON
Eindhoven	Personality	300	Personality	EXP
Eindhoven	Outpatient	150	Depression	CON
Eindhoven	Inpatient	104	Depression	EXP
Rivierduinen	Inpatient	35	Depression	EXP
Rivierduinen	Outpatient	240	Depression	CON

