### Intervention

In the experimental condition, the complete multidisciplinary teams (all registered nurses, psychologists, physicians, and psychiatrists) will be trained in the application of the guideline via the TtT-e program. By training complete multidisciplinary teams, including all team members, irrespective of full- or part-time staff, we aim for 100% coverage. In the TtT-e program, three types of actors are involved: masters, trainers, and trainees. The training is applied on two levels: first, trainers are trained by masters. Subsequently trainees are trained by trainers. The training program is supported by two e-learning modules. The first module is developed for trainees. It consists of video vignettes in which experienced nurses, psychologists, and psychiatrists interact with suicidal patients (played by actors). The total running time of this module for trainees is 60 minutes. In addition to the e-learning module for trainees, a second e-learning module was developed specifically for trainers. It provides a video of the first training session provided by masters to trainers, which was processed into an e-learning format allowing trainers to review the training session.

The TtT-e is a 1-day small interactive group program supported by e-learning modules, which reflects the PGSB recommendations
[1]. The PGSB recommendations served as the starting point to set the content of the TtT-e program within the PITSTOP suicide study. First, all guideline recommendations were listed and clustered into six themes: 1) basic clinical skills when discussing suicidality; 2) systematic assessment of suicidal behavior; 3) diagnosis of the current suicidal condition; 4) safety and continuity of care, including participation of the patient’s relatives; 5) treatment of suicidal behavior; and 6) chronic suicidal conditions. Second, clusters were transformed into six modules and scheduled according to the sequence of action in common clinical practice. For each module, goals and competences were set in terms of professional behavior. Furthermore, the PGSB recommends systematic investigation of the suicidal condition of patients by using the Chronological Assessment of Suicidal Events (CASE) interview

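### Staff who know the allocation judge, at their own discretion and after randomisation, whether a patient can complete the questionnaires; this leaves an avoidable risk that selection differs by arm

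*Protocol article*

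**What the plan says.** All statements are in the protocol article.

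- **Unit and time of allocation.** Departments are paired, and "Members of matched pairs were randomly allocated to either IAU" or the same plus the training programme (Randomization procedure).
- **Start of patient entry.** Entry follows allocation in both arms, at different points. For the experimental arm: "Measurements in the experimental departments will start immediately after all staff are trained". Control departments begin once they have been told which arm they are in (Measurement procedure).
- **Who knows.** "Healthcare professionals are aware of the allocation outcome, but patients are not" (Randomization procedure).
- **Who is trained.** In the experimental arm, "the complete multidisciplinary teams (all registered nurses, psychologists, physicians, and psychiatrists) will be trained" (Intervention). The themes include basic skills in discussing suicidality and its systematic assessment.
- **The patient-level exclusion.** "patients who are emotionally and/or cognitively unable to complete questionnaires properly will be excluded", followed by: "Whether a patient is able to enter the study will be left to the discretion of the staff" (Inclusion and exclusion criteria). No instrument or threshold is given.
- **What works against selection.** The same section includes patients whether or not they are suicidal at baseline. Measurement procedure says "we aim to reach all newly admitted patients in the participating departments", with data collected through routine outcome monitoring (ROM) or by graduate students and research assistants.
- **Primary comparison.** Statistical analyses compares changes in BSS scores between arms in multilevel models.

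**The concern.** Randomising departments makes the departments comparable in expectation. It does the same for the enrolled patients only if entry does not depend on allocation. Here the one stated patient-level exclusion is a subjective judgement, made after allocation by staff who know the arm and who, in one arm, have just been trained to engage with suicidal patients. Being emotionally unable to fill in a questionnaire is plausibly related to suicide ideation and to how it will develop.

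The direction cannot be predicted. Trained staff might more readily invite distressed patients, who have high scores and room to fall, which would look like a training benefit. They might instead shield such patients, which would mask a benefit. In either case the two arms could enrol different case mixes, and mean BSS change would differ without any effect of training. A larger sample does not remove such a bias.

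**Working it through.** **1. The sequence.** Set side by side, the statements give: department allocated; allocation known to staff; experimental team trained; patient admitted; staff judge ability; T0. The judgement comes after everything that distinguishes the arms.

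**2. The plan's own figure, for scale.** Inputs from Sample size: d = 0.3, alpha 0.05 (taken as two-sided), power 0.80, a 20% clustering correction, N = 423.
- n per arm = 2 × ((1.96 + 0.842)/0.3)² = 174.4, rounded up to 175; total 350.
- 350 × 1.20 = 420, close to the stated 423. The concern does not depend on this figure.

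**3. What a difference in case mix would do.** Every input here is an assumption; none is in the article. Suicidal patients: mean BSS 15, SD 8. Others: mean 1, SD 1. Suicidal patients fall 6 points and others 0, with no training effect. SD of change: 6. Suicidal share: 40% in one arm, 50% in the other.
- Variance of T0 at a 50% share = 0.5 × 1 + 0.5 × 64 + 0.25 × 14² = 81.5; SD = 9.0.
- T0 difference = 0.10 × 14 = 1.4 points = 0.16 SD.
- Spurious difference in change = 0.10 × 6 = 0.6 points.
- As d: 0.6/6 = 0.10 on the SD of change, or 0.6/9.0 = 0.07 on the SD of T0. The article does not say which SD defines its d. Against the target of 0.3 this is between about a quarter and a third.
- A 5-point difference in share halves these: 0.7 points at T0 and 0.3 points of change.

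**4. What linear adjustment for T0 would leave.** Same inputs, 50% share.
- Covariance of change with T0 = 0.25 × 14 × (−6) = −21; slope = −21/81.5 = −0.26.
- Remaining = 0.6 − 0.258 × 1.4 = 0.24 points, or d = 0.24/6 = 0.04. About 60% is removed.
- With an assumed slope of −0.3 within each group as well: covariance = −21 − 0.3 × 32.5 = −30.75; slope = −0.377; remaining = 0.6 − 0.377 × 1.4 = 0.07 points, or d about 0.01. About 88% is removed.

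**5. What that would do to the test.** Reading the 20% correction as a design effect of 1.2, the standard error of the standardised difference at N = 423 is √(2/(423/1.2/2)) = 0.107. With no true effect, the two-sided type I error is 1 − Φ(1.96 − b/0.107) + Φ(−1.96 − b/0.107) for a residual bias b:

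| Residual bias (SD) | Type I error |
|---|---|
| 0 | 0.05 |
| 0.04 | 0.07 |
| 0.07 | 0.10 |
| 0.10 | 0.16 |

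Step 4 covers only selection acting through suicidality, which T0 BSS measures. Selection on prognosis that T0 does not capture is not quantified, and the article gives nothing from which to quantify it.

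**The case against.** The strongest reply has four parts.

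- **The discretion is narrow.** It directly follows the exclusion of patients who cannot complete questionnaires, and the same paragraph includes patients regardless of suicidality. A reader might infer that staff may choose freely which patients enter, or may select on suicidality. The text does not support that; selecting on suicidality would breach the protocol. This stands and limits the point to the ability judgement.
- **Safeguards exist.** ROM or assistants aim to reach all new admissions, and the Discussion has assistants help patients complete the forms, which should make inability rarer. Patients do not know the allocation, so their consent should not depend on it. This reduces the risk, but the assistants are described as collecting data, while the entry decision is given to staff.
- **The mechanism is inferred.** No training theme concerns questionnaire ability, and the staff who decide are not defined. Treating staff is the likely reading, since Measurement procedure uses the word for the team that is trained. A reader might infer that the trial is biased, or biased towards the intervention; the documents show neither.
- **Knowledge of allocation and entry after it are largely inherent** in training teams and enrolling new admissions, and logs and model covariates are often left to a fuller document. Agreed: neither is faulted here. What is faulted is the stated rule that leaves a subjective eligibility judgement open to staff who know the allocation.

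**Conclusion.** The point holds as a risk of selection bias in the primary comparison. The article fixes an entry rule under which a subjective judgement, plausibly related to the primary outcome, is made after allocation by staff who know it. The stated aims of full coverage and of inclusion irrespective of suicidality lessen the risk but do not close it.

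The size is unknown. On wholly assumed inputs, a 10-point difference in the share of suicidal patients gives about 0.6 BSS points of spurious change (d about 0.07 to 0.1), of which about 0.24 points or less remains after linear adjustment for T0. The measured part of the problem is therefore mostly repairable in the analysis. The unmeasured part is not, and without counts of who was excluded and why it could hardly be detected or ruled out afterwards. The change should be made, but the point is no evidence that the trial's comparison is invalid.

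**What to change.** 1. Replace open staff discretion with short written criteria for inability to complete the questionnaires, identical in both arms.
2. Have the ROM or research assistants already in the plan apply them to consecutive admissions. Allow an exclusion by staff only with a recorded reason.
3. Keep a count per department of admissions, exclusions with reasons, and consents, and report these by arm.
4. State that the primary BSS comparison is adjusted for T0 BSS and does not rest on raw change alone.

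The article gives recruitment as ongoing, so items 1 to 3 can still be introduced for later admissions; the date of the change should be recorded. The cost is a one-page criteria sheet and a little logging time. The sample size does not change.

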### Randomization procedure

Eligible departments were clustered in pairs. It is assumed that similar types of patients treated for a similar duration of time are likely to be comparable. The first criterion for matching departments was the main diagnostic category of patients. For instance, a department that reported that 60% of the patients had a main diagnosis of depression was matched with another department that reported a comparable percentage of depressive patients. Within groups of comparable patient diagnoses, departments were matched with departments with comparable average treatment duration of patients. Members of matched pairs were randomly allocated to either IAU (internet, newsletter, books, publications, and congresses; control) or IAU with the TtT-e program (intervention). Randomization was performed by an independent researcher of the research institution (EMGO + Institute for Health and Care Research, Amsterdam, The Netherlands) who was not involved in the study. Table 
1 displays an overview of the types of departments, patient diagnoses, and results of the matching procedure. Healthcare professionals are aware of the allocation outcome, but patients are not.

**Table 1 T1:** Overview of the mental health institutions (MIHs), departments, main patient diagnoses, and results of the matching procedure

**MHI**	**Department**	**Average treatment duration of patients (days)**	**Main diagnosis**	**Condition**
Delfland	Inpatient	1,532	Depression	EXP
Delfland	Inpatient	1,308	Depression	CON
Delfland	Outpatient	624	Depression	EXP
Dimence	Outpatient	600	Depression	CON
Parnassia	Outpatient	21	Depression	CON
Parnassia	Inpatient	16	Depression	EXP
Delfland	Outpatient	740	Depression	CON
Parnassia	Inpatient	730	Depression	EXP
Pro Persona	Crisis	1	Depr/bord/crisis	CON
Pro Persona	Crisis	1	Depr/bord/crisis	EXP
Parnassia	Inpatient	250	Personality	EXP
Dimence	Inpatient	400	Personality	CON
Dimence	Crisis	1	Depr/bord/crisis	EXP
Parnassia	Crisis	1	Depr/bord/crisis	CON
Friesland	Outpatient	582	Depression	EXP
Friesland	Outpatient	814	Depression	CON
Friesland	Outpatient	743	Depression	EXP
Friesland	Outpatient	602	Depression	CON
Parnassia	Outpatient	90	Depression	EXP
Parnassia	Outpatient	21	Depression	CON
Viersprong	Personality	240	Personality	CON
Eindhoven	Personality	300	Personality	EXP
Eindhoven	Outpatient	150	Depression	CON
Eindhoven	Inpatient	104	Depression	EXP
Rivierduinen	Inpatient	35	Depression	EXP
Rivierduinen	Outpatient	240	Depression	CON
Parnassia	Outpatient	41	Depression (older adults)	EXP
Parnassia	Outpatient	Missing	Depression (older adults)	CON
Dimence	Inpatient	90	Depression	CON
Pro Persona	Outpatient	365	Depression	EXP
Altrecht	Outpatient	42	Depr/bord/crisis	EXP
Altrecht	Inpatient	150	Depr/bord/crisis	CON
Vincent van Gogh	Outpatient	172	Personality	CON
Vincent van Gogh	Outpatient	54	Personality	EXP
Rivierduinen	Inpatient	270	Personality	CON
Rivierduinen	Outpatient	180	Eating disorder	EXP
Viersprong	Outpatient	244	Personality	EXP
Parnassia	Outpatient	240	Addiction	CON
Rivierduinen	Crisis	Missing	Depr/bord/crisis	EXP
Rivierduinen	Inpatient	Missing	Personality	CON
Vincent van Gogh	Inpatient	96	Mood disorder NOS	CON
Vincent van Gogh	Inpatient	20	Schizophrenia	EXP
Parnassia	Inpatient	371	Depression (older adults)	CON

CON, control; Depr/bord/crisis, Depression/borderline/crisis; EXP, experimental; personality, personality disorder; MIH, mental health institution; missing, missing data; NOS, not otherwise specified.

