## Method

### Design

This is a multicentre cluster randomized controlled trial (RCT) in which multidisciplinary teams from mental health institutions (MHIs) are matched in pairs with respect to patient diagnoses and average treatment duration. Subsequently, pair members are randomly allocated to treatment conditions.

A MHI is a regional organization with a specific catchment area of patients
[24]. For example, in 2011, MHI Rivierduinen had a catchment area of 1.1 million people within an area of approximately 1,500 km^2^ in the region of South Holland. MHI Rivierduinen has 44 psychiatric departments and treats an overall number of 24,753 patients annually with 2,726 employees
[25]. Most of the psychiatric departments are specialized in the treatment of patients of specific diagnostic categories, such as depression or personality disorder.

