### Recruitment

Recruitment of MHIs took place during meetings and conferences on suicide prevention in The Netherlands between 2008 and 2010. MHIs were invited to participate in the study. When MHIs expressed willingness to participate, they were requested to indicate at least two multidisciplinary departments for adult care to be included in the study. To prevent exchange of training materials between the experimental and control condition, MHIs were explicitly asked to provide departments that were based in separate buildings and/or on separate locations, and to be sure that staff members were not exchanged or shared between departments. This resulted in 43 participating departments distributed over 10 MHIs (Figure 
1). Various types of mental health care departments are represented in the study (inpatient and outpatient care, crisis departments, and long-stay departments) treating patients of various diagnostic categories (personality disorder, depressive disorder, anxiety disorder, and psychotic disorder) and of various ages.

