#### Statistical analyses

As the study is a design with different levels, all outcomes will be analyzed using multilevel models. Patients are nested within departments (level 1), and departments are nested within MHI centers (level 2). Multilevel models are hierarchal systems that estimate random coefficients and variance components for each level
[33]. Random intercepts will be included in the multilevel models. Data will be analyzed on an intention-to-treat basis.

To examine the hypothesis that suicide ideation in patients of professionals who received the TtT-e program is more likely to be reduced than patients of professionals who did not receive TtT-e, we will compare changes in BSS scores between patients of teams allocated to the intervention with patients of teams in the control group. To examine differences in the number and intensity of suicide attempts, scores on items 20 and 21 of the BSS will be dichotomized (YES/NO, LOW/HIGH) and compared between treatment groups using logistic regression. To examine the effect of the intervention on treatment satisfaction, mean scores of the four satisfaction items between groups will be compared. For the economic evaluation, missing cost and effect data will be imputed using multiple imputation according to the MICE algorithm
[34]. The results of the imputed datasets will be pooled using Rubin’s rules
[35]. Bias-corrected and accelerated bootstrapping with 5,000 replications will be used to estimate 95% confidence intervals around the mean difference in total costs between the treatment groups. Incremental cost-effectiveness ratios (ICERs) will be calculated by dividing the difference in mean total costs between the treatment groups by the difference in mean effects between the treatment groups. Bootstrapping will also be used to estimate the uncertainty surrounding the ICERs, which will be graphically presented on cost-effectiveness planes. Cost-effectiveness acceptability curves will also be estimated. Cost-effectiveness acceptability curves will show the probability that the intervention is cost-effective in comparison with usual care for a range of different ceiling ratios (that is, the willingness to pay for one extra unit of effect)
[36].

Approval was obtained from the Medical Ethics Committee of the VU University Medical Centre, Amsterdam, The Netherlands (registration number: 2011/151). All local medical ethics committees agreed with this approval.

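### Pairs described as matched on main diagnosis differ on it in 4 of 21 cases, and care setting, never a matching criterion, differs in 8 of 21; the cost is precision, not demonstrated bias

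*Protocol article*

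**What the plan says.** The Design section of the protocol article says that the teams "are matched in pairs with respect to patient diagnoses and average treatment duration". The Randomization procedure section ranks the two factors: "The first criterion for matching departments was the main diagnostic category of patients", and then "Within groups of comparable patient diagnoses, departments were matched with departments with comparable average treatment duration of patients". The rationale is "It is assumed that similar types of patients treated for a similar duration of time are likely to be comparable". Table 1 is presented as the result of this matching and lists each department with its setting, average treatment duration, main diagnosis and arm. Neither section names care setting as a criterion.

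For the primary hypothesis, the Statistical analyses section says "we will compare changes in BSS scores between patients of teams allocated to the intervention with patients of teams in the control group". It uses multilevel models with random intercepts, with patients in departments and departments in institutions. It names no term for pair, setting or diagnosis. The one adjustment the article does promise, under Measurement procedure, is for the mode of data collection.

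**The concern.** The training is added to whatever care a department already gives. Ward, crisis and outpatient patients may well differ in starting ideation and in how much it changes over three months, trained team or not. Matching is meant to take such differences out of the comparison. It cannot do so for a factor that was not a criterion, or in pairs where the criterion was not met.

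Two things are at stake. First, the article describes its pairs as matched on diagnosis, and its own table contradicts this for some of them. Second, setting differences stay in the between-department variance, which lowers the power of a trial sized for a small effect (d = 0.3) with a modest allowance for clustering.

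**Working it through.** **Inputs.** Recruitment: "This resulted in 43 participating departments distributed over 10 MHIs". Table 1: 43 rows, 21 EXP and 22 CON. Sample size: 423 patients, d = 0.3, alpha 0.05, power 0.80, 20% correction for clustering. Table 1 prints no pair identifiers. I read rows 1–42 as consecutive pairs, which fits because each such pair holds exactly one EXP and one CON department. Row 43 is an unpaired control.

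**The plan's own figure.** Two-sided 0.05, power 0.80 and d = 0.3 need 175 per arm by the normal formula: 350 × 1.2 = 420. With 176 per arm (t-test), 352 × 1.2 = 422.4, rounded up to 423. So the 20% acts as a design effect of 1.2.

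**Discordant pairs, in table order.**

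| Pair | EXP | CON | Differs on |
|---|---|---|---|
| 3 | inpatient, depression | outpatient, depression | setting |
| 4 | inpatient, depression | outpatient, depression | setting |
| 12 | inpatient, depression | outpatient, depression | setting |
| 13 | inpatient, depression | outpatient, depression | setting |
| 15 | outpatient, depression | inpatient, depression | setting |
| 16 | outpatient, depr/bord/crisis | inpatient, depr/bord/crisis | setting |
| 18 | outpatient, eating disorder | inpatient, personality | both |
| 19 | outpatient, personality | outpatient, addiction | diagnosis |
| 20 | crisis, depr/bord/crisis | inpatient, personality | both |
| 21 | inpatient, schizophrenia | inpatient, mood disorder NOS | diagnosis |

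Setting differs in 8 pairs and diagnosis in 4. Two pairs differ on both, so 8 + 4 − 2 = 10 pairs differ on at least one and 21 − 10 = 11 on neither. Both members of pair 11 show Personality in the department column. Their setting is unknown, and the pair is counted as alike.

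**Direction and balance.** Of the 8 setting mismatches, EXP is inpatient against outpatient in 4, outpatient against inpatient in 3, and crisis against inpatient in 1. Arm totals, EXP v CON:
- inpatient 7/21 v 8/22
- outpatient 10 v 11
- crisis 3 v 2
- setting not stated 1 v 1

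Inpatient share by diagnosis, EXP v CON:
- depression departments, including older adults: 5/11 v 3/12
- all other departments: 2/10 v 5/10

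**Size.** Assume inpatient and crisis departments differ from outpatient departments by δ = 0.25 to 0.5 SD in BSS change. The share p that is inpatient or crisis, among departments with a stated setting, is (7 + 8 + 3 + 2)/41 = 20/41.
- Variance due to setting = p(1 − p)δ² ≈ 0.25 × 0.0625 = 0.016, up to 0.25 × 0.25 = 0.0625 SD².
- Allowance: 423/43 = 9.8 patients per department, about 10. From 1 + (10 − 1) × ICC = 1.2, ICC = 0.2/9 = 0.022.
- Ratio: 0.016/0.022 ≈ 0.7, up to 0.0625/0.022 ≈ 2.8.

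The article also states an average of 20 patients per department. At that size the same correction implies 0.2/19 = 0.011, so the comparison is less favourable still.

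**The case against.** The strongest reply is that a cluster-randomised trial needs balance in expectation, not identical partners, and the article supplies it: "Members of matched pairs were randomly allocated to either IAU" or IAU plus the training. With one department per arm, every department trait is inseparable from arm within a pair, matched or not. The mix of settings was deliberate, the mismatches run both ways and the totals are close. This stands.

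A reader might infer bias in the depression departments from 5/11 against 3/12 inpatient. The documents do not support that. It is a chance imbalance in a subgroup for which no analysis is stated, and the other departments lean the opposite way (2/10 v 5/10).

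A reader might also express the loss as a share of the variance of a pair difference. The stated model is not pair-based, and such a share would set all other department variance to zero, so I do not use it.

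It is also fair that covariates are commonly left to a statistical analysis plan, which is not shown here. The absence of a setting term is therefore not in itself an error. That does not answer the mismatch between the matching statement and Table 1, which lies within the article.

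Finally, 13 of 21 pairs share a setting label and 17 of 21 share the main diagnosis, so it would be wrong to say that the departments were not matched at all. In pair 20 the two diagnostic labels partly overlap.

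**Conclusion.** The point holds as a correction to the description of the matching and as an available gain in precision. The stated first criterion is not met in 4 of 21 pairs, and setting, which was not a criterion, differs in 8. The two counts overlap and should not be added to 12. In pairs 19 and 21 it is the patient group, not the setting, that differs. No bias in the whole-trial estimate is shown.

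On the assumed setting difference of 0.25 to 0.5 SD, setting alone would use about 70% of the clustering allowance, or exceed it nearly threefold. Neither the stated model nor the matching takes this variance out, so it falls to the department intercept.

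The counts rest on row order as the pairing. The size rests on the assumed difference, on treating crisis like inpatient care, and on reading the 20% as a design effect. If settings hardly differ in BSS change, the precision loss is small and only the wording correction remains.

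**What to change.** 1. In the primary BSS model and the secondary outcome models, prespecify department setting (inpatient, outpatient, crisis) as a fixed effect. First establish the setting of the two departments listed only as Personality.
2. Add a collapsed diagnosis factor, for example depression/mood, depression-borderline-crisis, personality, other. Do not use the eight raw labels: four of them (eating disorder, addiction, schizophrenia, mood disorder NOS) occur in one department each, and a single-department category would remove that department from the treatment contrast.
3. In the Design and Randomization procedure sections, state that 4 pairs are not alike on main diagnosis, and name them.
4. Optionally, report an analysis of the 11 pairs alike on both factors. It drops almost half the departments, so it can only be supportive.

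The cost is wording plus about 4 to 5 department-level degrees of freedom out of 43 departments (2 for setting, 2 to 3 for diagnosis). The two factors overlap, because all five crisis departments carry the depression-borderline-crisis label and only two other departments share it. Their separate coefficients should not be interpreted. The values are department characteristics that do not depend on outcome data, and the article reports recruitment as ongoing, so the choice can be fixed before outcomes are examined.
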